## Discussion

This protocol, following the Standard Protocol Items: Recommendations for Interventional Trials (SPIRIT) advice and Consolidated Standards Of Reporting Trials (CONSORT) 2010 guidelines, is designed to explore the synergistic effect of SAEM-CS on the recovery of motor function in patients in the acute stage of CI [36] (Additional file 4). We expect that rTMS will enhance the effect of SA and compensate for a commonly encountered problem in SA treatment: specifically, difficulty in twirling the acupuncture needle (as these needles should be twirled more than 200 times/min).

SAEM-CS is a treatment technique that combines LF-rTMS over the M1 region hot spot (motor cortex at the contralesional hemisphere) and SA stimulation of MS6 and MS7 at the upper limb regions of the lesional hemisphere to promote optimal functioning in patients following stoke. Despite other research showing that HF-rTMS applied to the lesional hemisphere more effectively improves motor function than LF-rTMS applied to the contralesional hemisphere in the early phases of stroke [9], LF-rTMS is selected for the combined SAEM-CS approach because there is some concern about complications that can arise due to the simultaneous use of SA and rTMS in the same hemisphere, and since we cannot completely exclude the interfering effects of HF-rTMS, even with non-magnetic needles. rTMS creates a powerful magnetic field near the stimulated area; therefore, all metal materials must be removed [37]. For rTMS and SA therapies that are conducted simultaneously (during SAEM-CS), we use a KOS-92 non-magnetic steel acupuncture needle that contains a much higher percentage of nitrogen (N) than STS304N1; thus, even in high processing volumes, the needle has no magnetic properties. The same method used in the SAEM-CS approach is employed for the SA and rTMS therapies. Thus, manual stimulation and electroacupuncture are not conducted in the SA group, and LF-rTMS is applied to the contralesional hemisphere in the rTMS group.

In the current study, we select patients hospitalized within 1 month after acute stroke in order to increase the homogeneity of the experimental population. This period was also chosen to increase reliability, because the most important period of recovery falls within the acute and subacute stages of ischemic stroke [38].

We expect that SAEM-CS will improve motor function; therefore, the FMA was selected as the primary outcome measure. In order to investigate unexpected effects of SAEM-CS, other scales assessing cognitive function, activities of daily living, walking, quality of life, and stroke severity are employed as secondary outcome measures.

Among TKM and CM professionals, there is a general lack of cooperation for developing techniques aimed to treat obstinate diseases. If the efficacy and safety of the above-described SAEM-CS approach is proven, it will serve as a model for collaborative research and will promote CM and TKM professionals to fuse therapeutic techniques. One hopes that such approaches can improve the treatment rates of incurable diseases.

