### Study design

This study is a prospective, outcome assessor-blinded, single-center, randomized controlled clinical trial with a 1:1:1:1 allocation ratio. This study is a pilot study to investigate the efficacy and safety of SAEM-CS, which is a newly developed treatment. This study is designed as a single-center study to overcome several procedural and organizational difficulties in terms of developing a research team, since SAEM-CS involves the simultaneous conduction of SA and rTMS. Participants (*n* = 60) who fit the inclusion and exclusion criteria will be randomly allocated into a control group (*n* = 15), SA group (*n* = 15), rTMS group (*n* = 15), and SAEM-CS group (*n* = 15). All groups will receive conventional stroke rehabilitation therapy twice/day, five times/week (excluding Saturdays and Sundays), for a total of 15 times over the course of a 3-week hospitalization period at Chonnam National University Hospital. In addition, the SA group will receive SA therapy, the rTMS group will receive rTMS therapy, and the SAEM-CS group will receive SAEM-CS therapy once/day. Outcome measures will be determined at baseline (before intervention), 3 weeks after the first intervention (end of the intervention), and 4 weeks after completion of the intervention.

This study was approved by the Ministry of Food and Drug Safety (MFDS), Medical Device Clinical Trial Plan Approval number 516. (See Additional file 1.)

The study design is summarized in Table 1 and Fig. 1.

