### Participant recruitment

For achieving adequate participant enrollment to reach target sample size, all stroke patients admitted to the Department of Neurology of Chonnam National University Hospital will be screened by Physical and Rehabilitation Medicine doctors. From among the first-ever patients with CI who are hospitalized and have finished treatment of early acute stage CI at the Department of Neurology, those who are assessed as stable by a neurologist and meet the inclusion and exclusion criteria will be recruited for participation in this study.

Patients who are given an explanation about this study by the Clinical Research Coordinator (CRC) and who voluntarily sign a consent form will be transferred to the Department of Physical and Rehabilitation Medicine to participate in this study (see Additional file 2). The CRC will continuously monitor the medical conditions of enrolled participants to improve adherence to intervention protocols.

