### Inclusion criteria

Patients who meet all of the following conditions will be considered for enrollment: patients who are aged >19 years; who have incipient CI confirmed by a computed tomography or magnetic resonance imaging examination; who are diagnosed by a neurologist or neurosurgeon; who experience a CI that resulted in motor and sensory disorders within 1 month of the study onset; who can undergo rehabilitation therapy after hospitalization in the Department of Physical and Rehabilitation Medicine, Chonnam National University Hospital; who have a modified Rankin Scale (mRS) score of 2–4; and who voluntarily sign an informed consent form.

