### Randomization

After signed informed consent and baseline measurements are obtained, random allocation software (developed by M. Saghaei, M.D., at the Department of Anesthesia, Isfahan University of Medical Sciences, Isfahan, Iran) is used to assign a serial number to the 60 research volunteers and to randomly allocate 15 of them into each group. The serial number codes will be inserted into sealed, opaque envelopes, kept in a double-locked cabinet, and opened in the presence of the patient and a guardian.

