### Data analysis

Continuous data will be presented as means and standard deviations, while categorical data will be presented as frequencies and percentages. A repeated measures ANOVA will be conducted for the FMA and all secondary outcomes (NIHSS, MBI, FIM, K-MMSE, 9HPT, ASHA-NOMS, FAC, EQ-5D, MAS, Hand Grip Strength, and MEPs). Dependent variables include measured values before and after intervention and the measured values 4 weeks after completion of intervention. An *F* test will be conducted to detect differences between therapies, and Tukey’s post hoc test will be conducted to identify the groups. Repeated contrast tests will be conducted to account for time differences in each group, and the interaction group and time test will be conducted. A *p* value of <0.05 will be considered significant, and participants who drop out of the study will be excluded from the analysis. In brief, only complete case analyses will be used; thus, only subjects who complete the three evaluations will be analyzed. All statistical analyses will be performed using SPSS version 22.0 software (SPSS Inc., Chicago, IL, USA).

Data from participants who engage in less than 70 % of protocol adherence (i.e., receive <10 treatments from 15 trials) will be eliminated. Missing values will be implemented by multiple imputations. In addition, statistical differences will be verified by comparing attribution between eliminated and completed participants to check particular factors causing drop-out.

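### Days since stroke onset probably predict FMA change within the 1-month entry window, but neither the allocation nor the stated FMA model uses them; adjusting would gain precision at little cost

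*Protocol article*

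**What the plan says.** **Entry.** Inclusion criteria admits patients "who experience a CI that resulted in motor and sensory disorders within 1 month of the study onset", which I read as infarction no more than 1 month before entry. No lower limit in days is given. Participant recruitment sets a practical one: patients must "have finished treatment of early acute stage CI at the Department of Neurology" and be judged stable by a neurologist.

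**Reasons for the window.** The Discussion gives two. The first is that "we select patients hospitalized within 1 month after acute stroke in order to increase the homogeneity of the experimental population". The second is reliability, "because the most important period of recovery falls within the acute and subacute stages of ischemic stroke".

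**Allocation.** Study design describes a "randomized controlled clinical trial with a 1:1:1:1 allocation ratio". Randomization says that software is used "to randomly allocate 15 of them into each group". No stratification or minimisation factor is named.

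**Analysis.** Data analysis states that "A repeated measures ANOVA will be conducted for the FMA and all secondary outcomes", using the three measurements, with an F test between therapies, Tukey comparisons, repeated contrasts and a group-by-time test. No covariate is named.

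**The concern.** If this period matters most for recovery, a patient starting in the first week and one starting near day 30 probably have different amounts of spontaneous recovery ahead of them. Repeated measures remove stable differences between patients in FMA level. They do not remove differences in slope, and slope is what the group-by-time test compares. Variation in slope that onset day could explain therefore goes into the error term, and a chance difference in onset day between arms moves the estimated treatment difference in the trial that is actually run. Arms are small: 15 are randomised, and Sample size works from 12 per arm before drop-out is added. Time since stroke has to be established for eligibility anyway, so the information is available but unused.

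**Working it through.** **1. The plan's own figure.** Sample size gives 4 groups, 3 measurements, f = 0.25, alpha 0.05 and power 0.80, for a total of 40. The within-patient correlation is not stated; I assume 0.5. For the group-by-time interaction, the noncentrality is f² × N × m / (1 − rho) = 0.0625 × 40 × 3 / 0.5 = 15, with (4 − 1)(3 − 1) = 6 and (40 − 4)(3 − 1) = 72 degrees of freedom. Power is 0.805, against 0.749 at N = 36. The 40 is reproduced and not disputed. It also shows that the trial was sized on the interaction, the test in which slope variation matters.

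**2. Chance imbalance in onset day.** The document gives no distribution of onset day, so I take three uniform spreads. SD = width / √12. The SE of a difference between two arm means is SD × √(2/n); for 0–30 days and n = 15 it is 8.66 × √(2/15) = 3.16 days. The gap between the earliest and latest of four arm means was simulated (50,000 trials).

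| Onset day | SD | SE of pairwise difference, n = 15 | Gap, n = 15: median / 95th percentile | Gap, n = 12: median / 95th percentile |
|---|---|---|---|---|
| 0–30 | 8.66 | 3.16 | 4.4 / 8.1 | 5.0 / 9.0 |
| 7–30 | 6.64 | 2.42 | 3.4 / 6.2 | 3.8 / 6.9 |
| 7–21 | 4.04 | 1.48 | 2.1 / 3.8 | 2.3 / 4.2 |

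These are gaps between the extreme arms; a typical pairwise gap is smaller.

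**3. Precision.** If onset day has within-arm correlation r with FMA change, linear adjustment multiplies the residual variance by 1 − r². The adjusted sample that matches 60 unadjusted patients is 60 × (1 − r²), before the small loss of degrees of freedom.

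| r (assumed) | Variance removed | Adjusted N equal to 60 unadjusted |
|---|---|---|
| 0.1 | 1% | 59.4 |
| 0.2 | 4% | 57.6 |
| 0.3 | 9% | 54.6 |
| 0.4 | 16% | 50.4 |
| 0.5 | 25% | 45.0 |

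**4. Type I error.** I simulated a simplified null model: one change score per patient, 15 per arm, onset uniform on 3–30 days, gain = 20 × exp(−t/12) plus normal error with SD 4, 6 or 10 (correlations −0.67, −0.52 and −0.35), 20,000 trials each. The curve is illustrative and not from the document.

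- All trials: 0.049 to 0.051 unadjusted and 0.049 to 0.050 adjusted.
- The 20% of trials with the largest onset imbalance: 0.15, 0.11 and 0.08 unadjusted, against 0.045 to 0.048 adjusted.

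The unadjusted test is valid over all randomisations. It misleads only in those that happen to be badly imbalanced.

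**The case against.** Three stronger readings are tempting, and the document supports none of them.

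- *The homogeneity statement is false.* The article claims only to increase homogeneity. A 1-month limit does that compared with a longer limit or none, so the sentence is true as written.
- *The two reasons for the window contradict each other.* The second is offered separately, for reliability. It calls the period the most important for recovery. It does not say that recovery is steepest there, or how fast expected gain changes between early and late entry.
- *The comparison is biased.* Randomisation protects it on average, and the ANOVA error already contains this variation. The raised error rates in step 4 appear only after selecting the most imbalanced fifth of trials.

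Beyond these, an unadjusted primary analysis is legitimate, the trial is described as an exploratory pilot, and an unseen analysis plan could list covariates. Entry after stabilisation also narrows the spread by an unknown amount. All the sizes above are assumed. If the total SD of FMA gain were 10 to 15 points and onset day contributed an SD of 1 to 5 points (both assumptions), it would explain between (1/15)² = 0.4% and (5/10)² = 25% of the variance, that is, from almost nothing to a useful share.

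Most of this stands, and it limits the point to efficiency and robustness. It does not remove it. Data analysis sets out its factors and tests in some detail without a covariate, and for a very small cost a better model is available from information that the trial must already hold.

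**Conclusion.** The point holds as an inexpensive improvement to the stated analysis, not as a flaw that invalidates it. Time since onset varies by up to a month, plausibly predicts the FMA change being compared, and enters neither allocation nor model. If its correlation with FMA change is 0.3 to 0.5, adjustment removes 9 to 25% of the residual variance, so about 55 to 45 adjusted patients would match 60 unadjusted. If the correlation is 0.1 to 0.2, the gain is only 1 to 4%. The earliest and latest arms would typically differ by about 2 to 4 days in mean onset at 15 per arm, and by about 2 to 5 days at 12. These figures rest on assumed onset-day spreads and correlations, because the document gives neither.

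**What to change.** In Data analysis, prespecify days from stroke onset to baseline assessment as a between-patient covariate in the FMA model, together with its interaction with time. The interaction is the part that acts on the group-by-time test. Alternatively, adjust the between-arm comparison of FMA change for the same variable. Centre it, so that the time effect refers to a patient at the average onset day, and report its distribution by arm. Fix this before outcomes are seen, because a covariate added after an imbalance is noticed would be data-driven.

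The cost is wording plus one to two degrees of freedom. With 60 patients, the between-patient error falls from 56 to 55 and the within-patient error from 112 to 110; with 48, from 44 to 43 and from 88 to 86. No new data are needed beyond recording the onset date that eligibility already relies on.

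The homogeneity sentence in the Discussion can stay. At most, qualify it to say that the window limits variation in time since stroke but does not remove it.

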### Dissemination policy

We will report the final data to the Ministry of Health and Welfare through the Korea Health Industry Development Institute, and we will publish the results at the end of this study.

### Trial status

This trial is ongoing. Enrollment and trial completion are expected to be finished by the end of May 2017.

## Abbreviations

CI: Cerebral infarction
SA: Scalp acupuncture
rTMS: Repetitive transcranial magnetic stimulation
SAEM-CS: Scalp acupuncture and electromagnetic convergence stimulation
CM: Conventional medicine
TKM: Traditional Korean medicine
FMA: Fugl-Meyer Assessment
NIHSS: National Institutes of Health Stroke Scale
MBI: Modified Barthel Index
FIM: Functional Independence Measurement
MMSE: Mini-Mental State Examination
ASHA-NOMS: American Speech-Language-Hearing Association National Outcomes Measurement System
FAC: Functional Ambulation Categories
EQ-5D: European Quality of Life-5 Dimensions
MAS: Modified Ashworth Scale
MEP: Motor evoked potential
mRS: Modified Rankin Scale
9HPT: 9-Hole Peg Test
